## **Duration and timeline**

The recruitment of all 70 participants is expected to be completed by July 2026, with data collection concluding by October 2026. The study results are anticipated in November 2026, and manuscript preparation is projected for completion by December 2026. The final manuscript will

be prepared following the CONSORT extension guidelines for pragmatic trials involving non-pharmacological interventions, as outlined in Fig 1.

## Statistical analysis

The analysis will follow the intention-to-treat, whereby all participants will be analyzed according to the groups to which they were originally randomized, regardless of their adherence to the intervention protocol. SPSS version 27.0 will be used to analyse all collected data. Missing data will be handled using multiple imputation, which creates several datasets by statistically estimating missing values and then combines the results to account for uncertainty. This method is preferred over last observation carried forward, as it reduces bias and more accurately reflects variability in clinical studies [61].

Descriptive statistics will summarize participants' baseline demographic and clinical characteristics. Continuous variables will be reported as mean (standard deviation, SD) or median (interquartile range, IQR) depending on the distribution, while categorical variables will be reported as frequency (percentage). Baseline comparability analysis of the clinical outcomes between groups will be performed using independent *t*-tests for continuous variables and Chi-square tests for categorical variables.

The primary outcomes (6MWT and MIP) and secondary outcomes (1MSTS, SPPB, hand grip strength, FSS, Bio-impedance Test, EuroQol, SAQ and Global Rating of Change Scale) will be measured at multiple time points: baseline, post-prehabilitation (4 weeks), before hospital discharge, and at 4 and 12 weeks postoperatively. To evaluate changes over time and between-group differences, a linear mixed-effects model (mixed model ANOVA) will be employed, provided the assumptions of normality and sphericity are met. Normality will be evaluated using the Kolmogorov–Smirnov test, while sphericity will be assessed using Mauchly's test. Mixed model ANOVA will provide results for time effect, group effect, and time-group interaction effect. Statistically significant time effect and group effect indicates significant within-group changes and between-group difference respectively, while significant time-group interaction effect determine if the interventions yield the desired effect on the dependent variables. Post hoc pairwise comparisons will be conducted using Bonferroni correction where appropriate.

The level of significance is set at  $p < 0.05$ . Effect sizes will be determined using Cohen's  $d$ , with values of 0.2, 0.5, and 0.8 indicating small, medium, and large effects, respectively [62]. Additional logistic regression will be used to determine preoperative, perioperative and postoperative risk factors associated with the development of respiratory complications. This will be an exploratory analysis, which may identify trends of predictors reported in the literature having an individual effect on postoperative respiratory complications. For all tests conducted, a  $p$  value of  $< 0.05$  (two-sided) will be considered statistically significant, and mean differences (95% CI) will be reported. The results of this study will be reported in accordance with the CONSORT 2010 guidelines.

|                                                                  | STUDY PERIOD                   |                                 |              |                                     |                                               |                                   |                              |
|------------------------------------------------------------------|--------------------------------|---------------------------------|--------------|-------------------------------------|-----------------------------------------------|-----------------------------------|------------------------------|
|                                                                  | Enrolment
& allocation      | Baseline                        | Intervention | Post-
intervention
assessment | Follow up                                     | Follow up                         | Follow up                    |
| TIMEPOINT                                                        | February
2025- July
2026 | 3-5 week
before
operation | 2- 4 weeks   | Preoperatively                      | Post-
operatively
prior to
discharge | 4-6 weeks
post-
operatively | 3 months post
operatively |
| Eligibility screen                                               | X                              |                                 |              |                                     |                                               |                                   |                              |
| Informed consent                                                 | X                              |                                 |              |                                     |                                               |                                   |                              |
| Allocation                                                       | X                              |                                 |              |                                     |                                               |                                   |                              |
| INTERVENTIONS                                             |                                |                                 |              |                                     |                                               |                                   |                              |
| Intervention A
(Interventional)                               |                                |                                 | X            |                                     |                                               |                                   |                              |
| Intervention B
(control)                                      |                                |                                 | X            |                                     |                                               |                                   |                              |
| ASSESSMENT                                                |                                |                                 |              |                                     |                                               |                                   |                              |
| Sociodemography                                           |                                |                                 |              |                                     |                                               |                                   |                              |
| Age                                                              |                                | X                               |              |                                     |                                               |                                   |                              |
| gender                                                           |                                | X                               |              |                                     |                                               |                                   |                              |
| Education                                                        |                                | X                               |              |                                     |                                               |                                   |                              |
| Occupation                                                       |                                | X                               |              |                                     |                                               |                                   |                              |
| Primary Measure                                           |                                |                                 |              |                                     |                                               |                                   |                              |
| 6 Minutes Walking
Test (6MWD)                                 |                                | X                               |              | X                                   | X                                             | X                                 | X                            |
| Maximal Inspiratory
Pressure (MIP)                            |                                | X                               |              | X                                   | X                                             | X                                 | X                            |
| Secondary
Measure                                     |                                |                                 |              |                                     |                                               |                                   |                              |
| Short Physical
Performance Battery
(SPPB)                  |                                | X                               |              | X                                   | X                                             | X                                 | X                            |
| 1 Minute Sit to
Stand (1MSTS)                                 |                                |                                 |              | X                                   | X                                             | X                                 | X                            |
| Hand grip Test                                                   |                                | X                               |              | X                                   | X                                             | X                                 | X                            |
| Bio-impedance Test                                               |                                | X                               |              | X                                   | X                                             | X                                 | X                            |
| Fatigue Severity
Scale (FSS)                                  |                                | X                               |              | X                                   | X                                             | X                                 | X                            |
| the Hospital Anxiety
Depression Scale
(HADS)               |                                | X                               |              | X                                   | X                                             | X                                 | X                            |
| Euro QoL (EQ-5D-
5L)                                          |                                | X                               |              | X                                   | X                                             | X                                 | X                            |
| Self-Administered
Physical Activity
Questionnaire
(SAQ) |                                | X                               |              | X                                   | X                                             | X                                 | X                            |
| Global Rating of
Change (GRC)                                 |                                | X                               |              | X                                   | X                                             | X                                 | X                            |

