The current literature highlights the significant impact of prehabilitation on improving patient outcomes in the context of major abdominal surgery. Prehabilitation programs incorporating aerobic, resistance, and breathing exercises, alongside education and lifestyle counselling, have been shown to enhance cardiorespiratory fitness, reduce postoperative complications, and expedite recovery. While moderate-intensity continuous training (MICT) is

commonly used in such programs, high-intensity interval training (HIIT) has emerged as a time-efficient and potentially superior alternative, particularly in improving VO2 max and preserving muscle mass.

Despite these findings, there is a lack of standardized exercise protocols tailored to the prehabilitation phase for patients undergoing major abdominal surgery. Additionally, limited data exist on the health status and functional outcomes of these patients throughout the surgical timeline. This gap warrants further investigation into the comparative effectiveness of HIIT and MICT, particularly in terms of their impact on multidomain recovery. By addressing these research gaps, this study protocol aims to provide valuable insights into optimizing prehabilitation strategies, ultimately improving the quality of care and recovery outcomes for patient

s undergoing major abdominal surgery.

Therefore, this study intended to evaluate the effectiveness of HIIT over MICT prehabilitation training on cardiorespiratory fitness and maximum inspiratory pressure among patients undergoing major abdominal surgery. This study also aims to investigate the effectiveness of HIIT versus MICT prehabilitation training on physical performances, upper limb strength, body composition, fatigue, psychological and health-related quality of life. We hypothesize that a 4-week HIIT program during prehabilitation is non-inferior to MICT in improving the targeted outcomes following major abdominal surgery, meaning the difference between the two interventions does not exceed the pre-specified non-inferiority margin ( $\Delta$ ).

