#### **1.4 Hypothesis**

- i. There will be variations in the standard of practice to these key questions across different states in Malaysia and among Malaysian physiotherapists in treating patients undergoing major abdominal surgery.
- ii. HIIT is non-inferior to MICT in improving cardiorespiratory fitness, maximum inspiratory pressure, physical performance, upper limb strength, body composition, fatigue, psychological recovery and health-related quality of life

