## **Blinding and allocation**

Patients and outcome assessors, will remain blinded to treatment allocation. However, the treating physiotherapists cannot be blinded due to the nature of the intervention. To maintain blinding, details of the intervention will not be recorded in the medical records. Outcome assessments will be conducted by a blinded assessor based off-site from the outpatient department, ensuring impartiality in both inpatient and outpatient settings. Intervention sessions will occur on different days from those scheduled for outcome assessments to further reduce the risk of unblinding. If a participant from the intervention group discloses details of their intervention to the assessor, this will be documented and reported, with the rationale recorded. All analyses will be performed on an intention-to-treat basis once randomization is unblinded.

Following recruitment and baseline assessments, participants will be randomly assigned to one of two groups which will be control group (MICT) or the intervention group (HIIT) using a computer-generated random number sequence. Allocation will be conducted by an independent individual utilizing a block randomization method (5 blocks of 14). An administrative assistant, independent of the trial, will prepare 70 sequentially numbered opaque envelopes, each containing a group allocation. A physiotherapist, trained in the study protocol, will deliver the intervention. Participants in the control group will receive moderate-intensity continuous training (MICT), while those in the intervention group will engage in high-intensity interval training (HIIT) preoperatively. Both groups will commence and conclude sessions with a warm-up and cool down to mitigate the risk of adverse events.

This study is will be conducted at a teaching hospital of the Hospital Canselor Tuanku Muhriz, Malaysia. Prospective consecutive patients will be invited to participate in the study prior to elective major abdominal surgery from February 2025 to July 2026. Fig 2 summarises the design of the trial, and each of the trial's aspect is described in detail below.

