## **Sampling and Size Calculation**

The sample size was calculated based on the primary outcome measure (6MWT). A recent systematic review of prehabilitation in patients undergoing major abdominal surgery reported significant improvement in 6MWT, with a mean difference of 29.4 meters (95% CI: 5.6 to 53.3 meters;  $p = 0.02$ ) compared to standard care [31]. The estimated standard deviation was approximately 101.6 meters, corresponding to an effect size (Cohen's  $d$ ) of 0.29. Using this effect size, with  $\alpha$  of 0.05 and power of 80%, the required sample size was calculated to be 54 participants. Allowing for a 30% dropout rate, a total of 70 participants (35 per group) will be recruited. Sample size calculation was performed using G\*Power version 3.1.9.7.

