## **Adherence monitoring**

Data related to exercise prescription, progression, complaints, injuries, and symptoms during training sessions for the both groups will be systematically recorded. Participants will be encouraged to adhere to the exercise guidelines outlined in their weekly flyers. Attendance will be documented, including the total number of sessions attended and successfully completed. Detailed reasons for incomplete sessions or participant dropouts will be recorded to evaluate non-compliance. Adherence to the prehabilitation exercise program will be closely monitored, alongside compliance with the prescribed exercise regimen. Additionally, participants will be asked to report the duration of their adherence and rate their adherence to home-based activities using a numerical scale [60].

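### Intention-to-treat regardless of adherence is the only analysis set behind a non-inferiority hypothesis, so nothing planned can show whether non-adherence produced the conclusion

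*Protocol*

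**What the plan says.** The Introduction states the hypothesis for the randomised phase: "We hypothesize that a 4-week HIIT program during prehabilitation is non-inferior to MICT in improving the targeted outcomes following major abdominal surgery". Section 1.4 repeats it: "HIIT is non-inferior to MICT in improving cardiorespiratory fitness, maximum inspiratory pressure", followed by the other outcomes. The Introduction explains the claim as meaning that "the difference between the two interventions does not exceed the pre-specified non-inferiority margin", but the protocol gives that margin no number.

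The Statistical analysis section analyses participants "according to the groups to which they were originally randomized, regardless of their adherence to the intervention protocol". The Blinding and allocation section is broader: "All analyses will be performed on an intention-to-treat basis once randomization is unblinded". No per-protocol or other adherence-based set is named.

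The data for such a set will exist. The Adherence monitoring section says: "Attendance will be documented, including the total number of sessions attended and successfully completed". It also has reasons for incomplete sessions and dropout recorded, so that non-compliance can be evaluated.

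**The concern.** In a superiority trial, non-adherence that blurs the contrast between arms usually makes the ITT test conservative. In a non-inferiority trial the same blurring moves the estimate towards no difference, which is the result that supports the claim. A narrow ITT difference could then mean that HIIT works as well as MICT, or that too few patients trained differently for a deficit to appear. With one analysis set, a reader cannot tell these apart.

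This is more than detail left to a statistical analysis plan. The protocol itself places all analyses on an ITT basis, so a later plan that added an adherence-based set would depart from its wording. The problem would also remain after a margin and a confidence-interval rule were added.

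**Working it through.** **Inputs from the protocol (Sampling and Size Calculation).** The 6MWT effect is a "mean difference of 29.4 meters (95% CI: 5.6 to 53.3 meters", for prehabilitation against standard care. The SD is 101.6 m and 35 patients per group are recruited. The stated effect size reproduces: 29.4 / 101.6 = 0.289, or about 0.29. The protocol gives no false non-inferiority rate to reproduce.

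**Assumptions.**
- Margin M: none is stated, so 29.4 m is used, with 50 m as a second value.
- Non-adherence q: no rate is stated, so 10% to 30% is shown. The protocol's own 30% is a dropout rate.
- Full-adherence HIIT deficit: set equal to M, so that any non-inferiority claim is an error.
- Rule: non-inferiority is declared if the two-sided 95% interval excludes a deficit of M (normal approximation). The protocol states no such rule.

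**Formulas.** Let b_M and b_H be the benefits of fully attended MICT and HIIT, with q_M and q_H the shares who gain nothing because they do not train.
- ITT deficit D = b_M(1 − q_M) − b_H(1 − q_H)
- SE = 101.6 × √(2/35) = 24.29 m
- False non-inferiority rate = Φ((M − D)/SE − 1.96)

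**Case 1: equal non-adherence.** D = (1 − q) × M.

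| q | D, M = 29.4 m | Rate | D, M = 50 m | Rate |
|---|---|---|---|---|
| 0% | 29.4 m | 2.5% | 50 m | 2.5% |
| 10% | 26.5 m | 3.3% | 45 m | 4.0% |
| 20% | 23.5 m | 4.3% | 40 m | 6.1% |
| 30% | 20.6 m | 5.5% | 35 m | 9.0% |

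For q = 30% and M = 29.4 m: (29.4 − 20.58)/24.29 = 0.363, and Φ(0.363 − 1.96) = 0.055.

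**Case 2: HIIT patients who train at MICT-like intensity.** If a share s of the HIIT arm responds as MICT patients do, D = b_M − [(1 − s)b_H + s·b_M] = (1 − s)(b_M − b_H). The shrinkage equals that in case 1, although all the non-adherence is in the HIIT arm. At s = 30% and M = 29.4 m, D is 20.6 m and the rate 5.5%. The design leaves room for this: the HIIT arm's week-one intensity is 55–75% of maximum heart rate, the band given for MICT, and the HIIT time per session depends on tolerance.

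**Case 3: unequal non-attendance.** Assume b_M = 60 m and b_H = 30.6 m, a deficit of 29.4 m, with M = 29.4 m.
- 30% in HIIT only: D = 60 − 0.7 × 30.6 = 38.6 m; rate 1.0%.
- 30% in HIIT and 15% in MICT: D = 51 − 21.42 = 29.6 m; rate 2.5%.
- 30% in MICT only: D = 42 − 30.6 = 11.4 m; rate 11.2%.

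The sign of the distortion therefore depends on which arm departs from its programme and on what those patients do instead.

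**The case against.** The best counter-argument concerns direction. The Literature Review cites a study in which patients adhered better to MICT because moderate intensity was familiar to them. If HIIT patients simply miss more sessions, case 3 shows ITT working against a non-inferiority claim. This stands, and it rules out saying that non-adherence always shrinks a HIIT deficit. It does not show that ITT alone suffices, because case 2 runs the other way and the protocol does not say which will dominate.

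It is also fair that the Duration and timeline section frames reporting as for a pragmatic trial, where the effect of assignment is a proper question. That supports ITT as the primary analysis, but not as the sole support for non-inferiority.

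Some stronger readings are tempting but go beyond the documents:
- A reader might infer that the hypothesis concerns a completed programme. It refers to a 4-week HIIT programme and does not restrict itself to completers.
- A reader might take the 30% in the sample size section as the expected share of untrained patients. It is dropout, and multiple imputation of missing outcomes does not by itself set the arm difference to zero.
- A reader might conclude that adherence data may not be used at all. The protocol intends to evaluate non-compliance; what it lacks is an adherence-based comparison of the arms.

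Finally, the missing margin and the reliance on two-sided difference tests are more basic gaps. That is true, but filling them would not resolve this point.

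**Conclusion.** The point holds in limited form. The protocol pairs a non-inferiority hypothesis with ITT as its only analysis set, and that set cannot show whether non-adherence helped or hindered the claim. The direction of any distortion is uncertain.

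The size cannot be derived from the protocol. On the assumptions above, equal non-adherence of 10% to 30% raises a nominal 2.5% error to between 3.3% and 5.5% at a 29.4 m margin, or between 4.0% and 9.0% at 50 m. With non-attendance in HIIT only, it can fall to 1.0%. The 29.4 m is borrowed from a comparison with standard care and is not proposed as a margin. A reader might infer that a false non-inferiority claim is the expected result; the documents do not support that.

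**What to change.** Amend the Blinding and allocation and Statistical analysis sections together:

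- Keep ITT as the primary analysis.
- Add a pre-specified supporting per-protocol analysis of the primary outcome (6MWT), adjusted for baseline 6MWT.
- Define adherence from the attendance log before unblinding. First reconcile the session prescriptions: the Abstract gives two sessions a week for at least four weeks, while both intervention sections give one to three a week over typically two to four weeks. No adherence threshold can be set while these conflict.
- Once the margin is stated, report both sets against it and interpret a non-inferiority conclusion cautiously if they disagree.

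Requiring both sets to succeed is one convention, but it is not recommended here as a hard rule. With no true difference and a 29.4 m margin, power is already only about 23% with 35 per arm: Φ(29.4/24.29 − 1.96) = Φ(−0.75). A double requirement would lower it further.

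The cost is some wording and one more analysis of data already being collected. The per-protocol set will be smaller, less precise and not fully protected by randomisation, so it should support ITT and not replace it.

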## **1.3. Objectives**

### **Primary Objective**

To determine the effect of HIIT over MICT on physical performance which is cardiorespiratory fitness (6MWT) and maximum inspiratory pressure among patients undergoing major abdominal surgery.

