## **Study Method**

### **Intervention care group (HIIT)**

Participants in the intervention group will receive the same care as the standard care group. Additionally, for aerobic exercise this will be a moderate intensity which is 55-75% of maximum heart rate (MHR) in week one, with graduation to high intensity in week two on > 80% of MHR [24]. Aerobic exercise training (eg: Treadmill, Cycle ergometer, body weight exercises) 1-3 times per week (30 minutes) for an overall duration typically 2-4 weeks prior to the date of surgery. Patients' Maximum Heart rate ( $210 - \text{age}$ ) and Karvonen Formula will be used for the targeted heart rate. Patients' heart rate will be monitored along the aerobic training using a smartwatch. However, those patients who are on beta-blockers or with underlying cardiac conditions, training intensity will be guided by the Rating of Perceived Exertion (RPE) between 16-18 RPE score, with appropriate adjustments made to ensure safety. The interval training will be 30-60 seconds of high-intensity training with 1- 2 minutes of active recovery (light activity or complete rest) between intervals to facilitate recovery. This will be repeated for a total of 5-10 cycles [32].

In addition to aerobic training, participants will receive the same progressive resistance exercise and inspiratory muscle training, with intensity matched to that of the standard care of

MICT group. Aim for a total session duration of about 20-30 minutes, including warm-up and cool-down. This includes 10-15 minutes of HIIT, depending on the patient's tolerance. Sessions will be done 1-3 times per week, with rest days in between to allow for recovery. Participants will also receive an illustrated handout to guide continued training support by caregivers, including recommendations on maintaining a standard amount of aerobic and strength exercise per week. A detailed session attendance checklist and vital signs will be recorded at each session to monitor adherence.

All other aspects of patient care such as preoperative management, general anaesthesia, intraoperative ventilation settings, fluid administration, prophylactic antibiotic use, pain management, management of lines and drains, general nursing care, and discharge planning will be administered at the discretion of nurses and physicians in accordance with routine clinical practices at hospital for both groups.

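### Two primary outcomes (6MWT and MIP) are tested at 0.05 with no rule for combining them, and only 6MWT enters the sample size

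*Protocol*

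**What the plan says.** Four places in the protocol make both outcomes primary:

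- Section 1.3, Primary Objective, names "cardiorespiratory fitness (6MWT) and maximum inspiratory pressure among patients undergoing major abdominal surgery" together.
- The section on primary outcome measures describes 6MWT and maximal inspiratory pressure (MIP), and no others.
- Statistical analysis (Phase 2) refers to "The primary outcomes (6MWT and MIP").
- The Fig. 1 schedule lists both under its primary-measure heading.

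Sampling and Size Calculation uses the singular: "The sample size was calculated based on the primary outcome measure (6MWT"). Its inputs all concern 6MWT. No effect, standard deviation or non-inferiority margin for MIP appears anywhere in the protocol.

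Statistical analysis sets one threshold for every test: p below 0.05 "two-sided) will be considered statistically significant, and mean differences (95% CI) will be reported". Its only multiplicity provision is "Post hoc pairwise comparisons will be conducted using Bonferroni correction where appropriate". It gives no order of testing and no split of alpha between the primaries, and it does not say whether one or both must succeed.

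On treatment, the HIIT section says that "participants will receive the same progressive resistance exercise and inspiratory muscle training", at an intensity matched to the MICT arm. The MICT section sets the inspiratory training at 20 minutes per day at 30% of MIP.

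**The concern.** With two primary outcomes, a trial needs a rule that turns two test results into one conclusion. This protocol has none, and the two obvious rules have different consequences. If a positive result on either outcome is enough, the chance of a false claim exceeds the nominal 5%. If both must be positive, alpha is safe but the power of the trial is the joint power, and one of the two outcomes was never sized. Without a stated rule, the choice can be made after the results are known.

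The choice of MIP as a primary adds a question of interpretation. The training aimed directly at inspiratory muscle strength is the same in both arms. Only the aerobic component differs, so any true difference in MIP has to come through that route.

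**Working it through.** **Inputs.** Two primary outcomes, each tested at two-sided 0.05, with no adjustment between them (Statistical analysis). For 6MWT: difference 29.4 m, SD 101.6 m, 80% power, 54 evaluable, 70 recruited (Sampling and Size Calculation). For MIP: nothing. The correlation between the two test statistics is not given, so I assume a range from 0 to 0.9.

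**Step 1: the plan's own figure.** d = 29.4 / 101.6 = 0.289. For a plain two-group comparison, n per arm = 2(z for alpha + z for power)² / d².

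- Two-sided: 2 × (1.960 + 0.842)² / 0.289² gives 188 per arm, 376 in total.
- One-sided: 148 per arm, 296 in total.

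The stated 54 is not reproduced. A repeated-measures calculation with f = d/2 = 0.145, five measurements and an assumed correlation of 0.5 gives 58. This is a separate problem, and nothing below depends on it. What matters here is that every input is a 6MWT figure.

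**Step 2: either primary suffices.** For independent tests with no true difference on either outcome:

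P(at least one false positive) = 1 − (1 − 0.05)² = 1 − 0.9025 = 0.0975.

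For correlated tests, I used a simulation of two million bivariate normal pairs, counting those with either value beyond ±1.96:

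| Assumed correlation | P(at least one false positive) |
|---|---|
| 0 | 9.75% (exact) |
| 0.3 | 9.5% |
| 0.5 | 9.1% |
| 0.7 | 8.3% |
| 0.9 | 7.0% |

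These figures are for two-sided tests of difference, which is how Statistical analysis is written. If non-inferiority were instead judged from the reported 95% CI, the error per outcome would be 2.5%. The either-suffices figure would then be 1 − 0.975² = 4.9% under independence, the same near-doubling from a lower base.

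**Step 3: both primaries required.** A false overall claim needs a false positive on at least one outcome together with a positive on the other, so the error rate stays at or below 5%. The cost is power. As a purely hypothetical case, two independent outcomes each powered at 80% have joint power 0.80 × 0.80 = 0.64. For this trial the figure cannot be computed, because no MIP effect is given.

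**Step 4: what MIP can show.** Inspiratory muscle training and resistance exercise are matched. Aerobic intensity, duration and mode differ. A MIP difference beyond chance could therefore arise only indirectly, through the aerobic work. A small difference fits two explanations equally well: HIIT does as well as MICT, or the shared inspiratory training dominates in both arms.

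**Step 5: check of a fixed sequence.** Test 6MWT at 0.05, and test MIP at 0.05 only if 6MWT succeeds. If there is no true 6MWT effect, any false claim must first pass the 6MWT test, which has probability at most 5%. If the 6MWT effect is real, only MIP can yield a false claim, again with probability at most 5%. The family-wise rate for the two outcomes is 5% with no alpha split. By contrast, a Bonferroni split at 0.025 each raises the two-group sample size in Step 1 from 376 to 456 (456 / 376 = 1.21).

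**The case against.** The best defence is that the protocol joins its outcomes with a conjunction. The primary objective links 6MWT and MIP in that way, and section 1.4 lists all outcomes in one non-inferiority hypothesis. On that reading both must succeed, and testing each at 0.05 inflates nothing. This is a fair reading, and it is why the inflation in Step 2 has to be stated conditionally. It does not remove the point: the protocol never says that this is the rule, and the size calculation treats 6MWT as the only primary.

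A second defence is that an unseen statistical analysis plan may supply the rule. That has limited force, because the protocol itself fixes 0.05 for all tests and confines Bonferroni to post hoc pairs.

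A third is that MIP is a legitimate outcome. Aerobic training may affect respiratory function, and asking whether HIIT differs from MICT in this respect is reasonable. That stands. The recommendation rests on the missing rule and the missing design basis, not on MIP being a poor measure. Sizing a trial on one of two primaries is not in itself an error either.

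Three stronger readings are tempting, and the documents do not support them:

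- A reader might count the group effect and the time-by-group interaction as two routes to success for each outcome, giving four tests and a larger error rate. Statistical analysis ties the desired effect of the interventions to the interaction, so one efficacy test per outcome can be identified.
- A reader might compute a very low joint power by giving MIP the 6MWT effect size. The protocol gives no MIP effect, and matched inspiratory training argues against borrowing one.
- A reader might say that the arms receive identical training. That is exact for the inspiratory and resistance work, but not for the aerobic work.

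**Conclusion.** The point holds in a limited form. The protocol contradicts itself on the number of primary outcomes, and its stated testing rule leaves the two primaries without joint control.

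- **If either counts:** the chance of at least one false-positive primary is 9.75% under independence and about 7% to 9.5% at assumed correlations of 0.9 to 0.3, for two-sided tests of difference at 0.05.
- **If both are required:** alpha is controlled, but joint power falls below that for 6MWT alone by an amount that the documents do not allow one to compute.

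It would be too strong to say that the trial's error rate is doubled, since that assumes an either-suffices rule that the protocol does not state. It would also be too strong to say that MIP is bound to look non-inferior. Matched inspiratory training pulls the difference towards zero, but no margin is given, so the tendency cannot be quantified. What can be said is that a small MIP difference would be weak evidence about HIIT.

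**What to change.** Make 6MWT the single primary outcome, in line with Sampling and Size Calculation, and make MIP the first key secondary outcome. Change section 1.3, the section on primary outcome measures, Statistical analysis and the Fig. 1 schedule to match. Wording such as this would do:

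> The primary outcome is 6MWT distance, compared between groups at [one named visit]. MIP is the first key secondary outcome. It is tested at the 0.05 level, on the same contrast, only if the 6MWT comparison meets its success criterion.

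Define the success criterion for whichever hypothesis is kept. For superiority it is a significant difference. For non-inferiority it is a confidence limit inside a stated margin, and each of the two outcomes then needs its own margin. Name the contrast in advance and use the same one for both outcomes.

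This needs no extra participants. The scientific cost is that MIP cannot be claimed on its own if 6MWT fails. The administrative cost is more than editing: Blinding and allocation has patients invited from February 2025, and the ethics approval letter requires approval of all changes. The revision should therefore be a dated, ethics-approved amendment made before unblinding, with the registry entry updated to match.

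If the sponsor prefers to keep two primaries, the minimum is to state whether both or either must succeed. An either rule also needs an alpha split or a testing order. A both rule needs an effect or margin and an SD for MIP, so that joint power can be given.
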